### Randomization

Participants will be assigned to one of two groups according to a computer-generated randomization list (computerized random numbers). As such, participants will be randomly assigned with a 1:1 allocation ratio following permuted block design procedures, using block sizes of four. No stratification criteria will be used. The allocation sequence will be generated by an independent researcher not involved in this project after baseline measures, thus ensuring that therapists and recruiters are kept blind to the allocation of each participant. The allocation sequence will be password protected and only accessible by the independent researcher. The research assistant responsible for the logistics of this project - who is not part of the treatment team - will not be kept blind for allocation and will be responsible for contacting participants randomly assigned to the experimental condition.

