### Participants

Based on prior studies testing cognitive-behavioral interventions in adolescents with cancer, eligible participants are adolescents aged 11 to 18 years with a diagnosis of cancer
[23-25]. In keeping with previous research, there will be no specific selection/exclusion based on type, stage, or trajectory of cancer
[11,26-28]. The intervention will be conducted in French. Therefore, participants are required to speak and understand the language. They must be willing to participate in an 8-week mindfulness meditation program and be available to complete the measures 6 months after the intervention. They must not have a diagnosis of severe mental illness.

Based on prior mindfulness intervention studies with adolescent populations and on usual number of participants in a mindfulness-intervention training group (as indicated by Kabat-Zinn and colleagues
[29] in the MBSR program) a final sample size of 28 participants is targeted
[13,29-33]. Taking into consideration attrition rates from prior research (20-30%), an additional 12 participants will be recruited
[2,34-36]. Thus, a total of 40 participants will be recruited. Participants will be randomly assigned to the experimental or control group, and immediately given a participant ID for confidentiality and anonymization purposes. Twenty adolescents will be completing the mindfulness meditation intervention, which will be taught by two trained therapists (doctoral clinical psychology student and psychiatrist). The intervention will comprise of eight weekly sessions, lasting 90 min each.

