### Screening procedures, consent to participate, and enrollment

One of two screening and enrollment procedures has been applied, depending on the modality of first contact with potential candidates for the project. When contacted by telephone by teenagers having heard of the project and interested in participating, researchers summarize the study, and a meeting is scheduled to complete screening procedures, sign the consent forms, and complete pre-intervention measures. When participants are recruited directly on site, screening, consent, enrollment, and pre-intervention measures are completed immediately. Participants are informed of the possibility of a delay (a few weeks up to a few months) before starting the intervention, as participants continue to be recruited. Informed consent will be obtained by all recruited participants. Intervention will begin either when: (1) 20 participants are selected to be in the experimental group; or (2) 10 participants are selected to be in the experimental group (thus implying that two experimental groups of 10 participants will be run), depending on recruitment speed and efficiency.

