## Trial status

This is a clinical trial with ongoing patient recruitment. Recruitment for this project started in September 2012, and is expected to be completed by May 2013. This trial is recorded under the number NCT01783418.

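### A single list with a fixed, published block size of four makes some assignments predictable to anyone who knows all earlier ones; batch allocation or undisclosed varying blocks would remove most of this risk

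*Protocol article*

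**What the plan says.** All references are to the protocol article.

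- **Randomization.** The allocation ratio is fixed ("participants will be randomly assigned with a 1:1 allocation ratio"), blocks have one size ("following permuted block design procedures, using block sizes of four") and there are no strata ("No stratification criteria will be used"). A researcher outside the project generates the sequence after baseline and alone can open the password-protected file. The section says this keeps recruiters and therapists blind. The research assistant who handles logistics, and who is outside the treatment team, "will not be kept blind for allocation and will be responsible for contacting participants randomly assigned to the experimental condition".
- **Participants.** "Thus, a total of 40 participants will be recruited", against a target after attrition of 28 ("a final sample size of 28 participants is targeted").
- **Screening procedures, consent to participate, and enrollment.** The programme starts either when 20 are in the experimental arm or when "10 participants are selected to be in the experimental group". In the second case there are two experimental groups of 10. Participants are warned that they may wait weeks to months while others are recruited.
- **Recruitment.** Recruitment takes place in the oncology centre of one hospital. Physicians, nurses and research nurses introduce the project.
- **Trial status.** "This is a clinical trial with ongoing patient recruitment".

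**The concern.** With one centre and no strata, a single list runs through all participants. Because every block holds two experimental and two control places, anyone who knows the assignments so far can work out part of what follows.

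Password protection and independent generation hide future entries on the list. They do not hide assignments already made. The research assistant knows allocations. Participants assigned to the programme know their arm once contacted. Therapists learn who is in the experimental group at its first session, so the statement that they are kept blind cannot hold after that point. Under the two-group option, the first group of 10 may start while recruitment is still open.

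The stake is selection bias. Staff who can foresee the next assignment could time or steer an approach to a patient. In a trial that aims for 28 completers and does not restrict cancer type, stage or trajectory, a few steered enrolments could make the arms differ. There is a second, smaller stake: if allocation precedes a wait of weeks to months, participants can be lost after randomisation but before the programme begins.

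**Working it through.** **Inputs.** Block size 4, ratio 1:1, no strata (Randomization). 40 recruited, 28 targeted after attrition of 20-30% (Participants). First start possible at 10 experimental participants (Screening procedures).

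**The plan's own figure.** 28 / (1 - 0.30) = 40, which matches the stated total (28 + 12). At 20% attrition, 28 / (1 - 0.20) = 35. Forty participants make 40 / 4 = 10 complete blocks. The article gives no figure for predictability.

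**Upper bound: all earlier assignments and the block boundaries known.** A block has 6 equally likely orders of two experimental and two control places.

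| Place in block | Chance that it is certain | Chance that the best guess is right |
|---|---|---|
| 1st | 0 | 1/2 |
| 2nd | 0 | 2/3 |
| 3rd | 1/3 (first two alike) | 1/3 × 1 + 2/3 × 1/2 = 2/3 |
| 4th | 1 | 1 |
| Sum | 4/3 | 17/6 |

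- Certain assignments: (4/3) / 4 = 1/3, or 40 / 3 = 13.3 of 40.
- Correct guesses: (17/6) / 4 = 17/24 = 70.8%, against 50% under simple randomisation.

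**Allocations learned only when the first group of 10 starts.** Each block supplies two experimental places, so the 10th experimental assignment falls in block 5. All that can be deduced is the run of control places left in that block. Over the 6 orders, the number left is 2, 1, 1, 0, 0, 0. The mean is 4/6 = 2/3 of one assignment, or 0.67 / 40 = 1.7% of the total.

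**Is allocation sequential?**
- For: the start is triggered by a count of people already in the experimental arm, while others are still being recruited. A batch scheme would more naturally count people who have consented.
- Against: generating the sequence after baseline also fits batch allocation of a complete cohort. Twenty participants are exactly 20 / 4 = 5 blocks, giving 10:10.

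Sequential allocation is the more natural reading, but it is an inference. Under batch allocation nothing could be predicted at enrolment.

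**Effect of other block schemes, all earlier assignments known.** For a fixed block of size 2m, the certain share is 1/(m + 1): 1/4 (10 of 40) for blocks of 6 and 1/5 (8 of 40) for blocks of 8. For sizes drawn at random, with the set of sizes known but their order concealed, simulation of 4,000 sequences of 40 gives about 5.6% for {4, 6}, 4.1% for {2, 4, 6} and 2.3% for {4, 6, 8}. These figures count certain deductions only; some better-than-even guessing would remain.

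**The case against.** The strongest reply is that the documents place no fully informed person among those who enrol. Recruiters are stated to be blind. Apart from the independent researcher, the only role stated to be unblinded is a logistics assistant with no stated part in enrolment. Patients arrive by several routes (clinicians, record screening, posters, a newsletter, telephone self-referral). Following the list would therefore require the order of randomisation across all of them, controls included. If the single-start option is used, 20 experimental participants at 1:1 imply about 40 randomised before anyone attends, so attendance then reveals almost nothing useful. Fixed blocks also keep a small pilot close to 20:20.

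Most of this stands, and it limits the size of the point. A reader might infer that clinic staff can in practice deduce a third of the assignments, or that concealment has been broken. The documents support neither. Allocation is never stated to be sequential, and the one leak that follows directly from the text, attendance at the first group of 10, yields 2/3 of one assignment rather than 13.

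The reply does not remove the weakness. The safeguards protect future entries, whereas the block structure leaks through past ones. Participants and therapists learn those as soon as a group starts. The attrition allowance covers numbers lost, not differences between arms in who is lost.

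**Conclusion.** This is a modest, avoidable weakness in allocation concealment. The fixed block size, the single list and its disclosure during open recruitment are stated facts. The predictability of 1/3 certain (13 of 40) and 71% guessed correctly is exact, but it is an upper bound. It requires sequential allocation and an observer who knows the block boundaries and every earlier assignment in order. For an observer who learns allocations only at the first group's start, the figure is less than one assignment on average. The true exposure depends on how far past assignments become known to recruiting staff, which the article does not allow one to estimate. The argument about losses between randomisation and the programme also depends on allocation being sequential.

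**What to change.** For participants not yet randomised, either of these changes to the Randomization section would do:

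1. **Batch allocation (preferred).** When about 20 participants have consented and completed baseline, the independent researcher allocates the whole cohort 10:10 just before the first session. Nothing can then be predicted at enrolment, and the gap between randomisation and the programme shortens. The programme already waits for a full group, so little time is lost. The start rule should then count participants with consent and baseline complete.
2. **Sequential allocation with varying blocks.** The independent researcher draws the remaining list with randomly varying block sizes that are not disclosed to recruiting staff.

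In both cases the section should say whether assignment is sequential or by batch and who can see past assignments during recruitment.

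The cost is a wording change and a new list. With varying blocks the arms may differ by a few participants: stopping inside a block of 6 leaves a difference of at most 3, and inside a block of 8 at most 4. Recruitment was expected to finish by May 2013, so the change helps only those still to be randomised.

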### Wait-list

The use of a wait-list control condition has been compelling in past studies on MBSR and cancer to test for the effectiveness of the intervention without compromising recruitment, while favoring retention of participants who will later benefit from the intervention
[36,37]. Once the follow-up assessment has been completed with the experimental group, wait-list controls will be offered to complete the mindfulness-based program. The data collected on these participants through the second round of intervention will also be analyzed to test the mindfulness-based intervention.

### Experimental group

The present mindfulness-based meditation intervention is inspired by protocols designed at the Centre de consultation psychologique specialisé of the Université Catholique de Louvain (Belgium)
[38], as well as by Biegel and colleagues
[39]. The intervention will be led by two trained therapists (psychologist and psychiatrist), alternating roles (leader *vs.* co-leader) at each session, leading a total of four sessions each. In accordance with the initial MBSR program designed by Kabat-Zinn and colleagues
[5], the mindfulness-based intervention will last 8 weeks, the group meeting once a week and each session lasting 90 min. Based on previously cited protocols designed for youth, no silent retreat will be included in this intervention.

### Mindfulness-based intervention protocol

#### Week 1

The mindfulness intervention will begin with an overview of class rules and the 8-week program. Participants will present each other in dyads, then to the whole group. They will also be asked to write down expectations and intentions in regards to the intervention (these will be collected by the therapists and handed back to all participants at the last session). An introduction to mindful eating with a cranberry tasting exercise will take place. Home practice for this session will include completing mindful tasks during the week and a ‘thinking outside the box’ exercise. A minimal practice of 30 min each week, followed by an entry in their weekly meditation journal will be suggested to participants.

#### Week 2

Participants will be guided through a body scan meditation. An introduction to the different components of emotions (that is, thoughts, physical sensations, behavior) and stress, as well as their effect on the body and mind will be discussed. An outstretched arms meditation will be completed, in order to practice mindfulness through pain. Home practice will include familiarization with the body scan and cultivating mindfulness of the body.

#### Week 3

Participants will be guided through a breathing meditation and will be introduced to sitting meditation. Mindful movements will also be introduced, through gentle yoga-like poses inspired by readings from *Mindful Movements: Ten Exercises for Well-Being*[40]. Home practice will include sitting meditation and mindful breathing in the context of pleasant and unpleasant events.

#### Week 4

Participants will be guided through a breathing meditation. Concepts of acceptance of thoughts, emotions, and bodily sensations will be discussed. In dyads, participants will be asked to exchange about suffering. During this activity, they will be asked to stop periodically and do a mindful check-in of how they are feeling while discussing a difficult topic. Home practice will include sitting meditation and the reading of Rumi’s *The Guest House* poem.

#### Week 5

Participants will be guided through a breathing meditation, with a special focus on thoughts and judgments. Mindful senses will then be explored, mainly through mindful touching and breathing. Participants will complete an inhibition activity and will be asked to reflect on our natural propensity to have spontaneous negative thoughts and judgments and discussing how we can come to inhibit such thoughts. Home practice will include meditation on thoughts and judgments.

#### Week 6

Participants will be guided through a heartfulness meditation, with a special focus on self-care and sending compassion to others. A group discussion on the topic of self-care *vs.* selfishness will take place. The concept of acceptance will also be explored. The session will end with a short sitting meditation with an emphasis on acceptance. Home practice will include heartfulness meditation and mindful activities that provide self-care.

#### Week 7

Participants will be guided through the mountain meditation. In dyads, participants will be asked to recall an autobiographical memory and identify how this memory reflects their personal values. A group discussion on personal and life values will then take place. Participants will be asked to reflect whether mindfulness can be considered as a value or a tool in living in accordance with our personal values. Home practice will include any type of meditation practiced in the previous weeks, as well as a reflecting on the importance of being mindful while acting accordingly to personal values.

#### Week 8

Participants will have the choice of the type (sitting *vs*. lying down) of meditation and special focus they want to bring to the practice. Intentions set at the first session will be redistributed to all participants. Participants will be given the opportunity to exchange about the intervention and give comments and feedback to the therapists. A giant puzzle activity will take place, in which participants will be asked to write on each piece personal benefits and/or disadvantages of the intervention and their meditation practice. The session will end with the distribution of a pebble stone to each participant as a reminder of their experience.

### Measures

#### Assessment time-points

Measures will be completed by all participants (that is, experimental and control group) at three moments in time: (1) baseline, after the screening interview, consent forms are signed and enrollment is confirmed; (2) immediately post-intervention, at the end of the eighth session; and (3) at 6 months follow-up, when questionnaires will be sent out by mail. At each time period, participants will fill out the questionnaire package, taking approximately 60 min to complete. There will be time allocated at the first and last sessions to complete questionnaires on site. After the third assessment period, once the last questionnaire package has been sent back to the research team, a $10 iTunes gift cards will be mailed to each participant to thank him/her for his/her participation. All measures and corresponding assessment time-points are illustrated in Figure 
2.

**Figure 2 F2:**
[figure not shown]
Measures and assessment time points.

### Primary outcome measures

Beck Youth Inventories™ - Depression and anxiety scales
[41]: this measure will be used to evaluate symptoms of depression and anxiety. Each scale comprises 20 items, for which participants are asked to indicate on a Likert-type scale ranging from 0 (‘never’) to 3 (‘always’) how frequently each statement applied to them in the past two weeks. Both scales have presented excellent internal consistency (α >0.84) and good reliability (r >0.73) for adolescent populations
[42]. For the purposes of this project, a validated French version will be used
[43].

Positive and Negative Affect Schedule - Child (PANAS-C)
[44]: this measure is used to evaluate the presence and fluctuations in positive and negative emotions. The questionnaire comprises 20 items, for which participants are asked to answer on a Likert-type scale ranging from 1 (‘not much or not at all’) and 5 (‘a lot’), whether the described emotion matches what they have felt like in the past few weeks. This measure presents excellent results in terms of internal consistency (α ranging from 0.91 to 0.92) and good reliability for adolescent populations
[45]. A French version has been validated, and will be used for this project
[46].

Pediatric Cancer Quality of Life Inventory
[47]: this measure is used to evaluate quality of life in children and adolescents with cancer. The questionnaire comprises 27 items for which participants are asked to indicate on a Likert-type scale ranging from 0 (‘never’) to 4 (‘almost always’) how much each symptom has been problematic in the past month. The measure has good to excellent psychometric properties in terms of construct validity, reliability, internal consistency (α = 0.91 to 0.92) and clinical validity
[47]. A French version of this questionnaire is available and will be used for this project
[48].

Pittsburgh Sleep Quality Index
[49]: this measure evaluates sleeping habits in the past month. The questionnaire comprises 11 items, and presents good psychometric properties in terms of internal consistency (α = 0.83), test-retest reliability (r = 0.85), and convergent validity
[49]. This measure is commonly used with adolescents and is validated in French
[50-52].

### Process measure

Children and Adolescent Mindfulness Measure
[53]: this measure is used to evaluate mindfulness in children and adolescents. The questionnaire comprises 25 items, for which participants are asked to indicate on a Likert-type scale ranging from 0 (‘never true’) to 4 (‘always true’) how often each item is true for them. This measure is included in the project in order to assess the extent to which adolescents become more mindful as they receive the intervention, as well as to control for existing differences between participants in their natural tendency to embody mindfulness concepts. The measure presents good internal consistency ( α = 0.87), as well as good convergent validity, and is available in French
[53].

In addition, in-house social support analog scales presently in development will be administered, in order to evaluate if any improvements on quality of life, mood, and sleep can be linked to social support and the overall social nature of the intervention.

### Planned statistical analyses

Descriptive statistics on participant characteristics will be presented for each group at baseline. Means and standard deviations on primary and secondary outcome variables will be presented for each group at 8 weeks and 6 months.

The cut-point to reject the null hypothesis will be set at 5% (α ≤0.05). Primary hypotheses will first be tested using three mixed analyses of covariance (ANCOVA) with Bonferonni corrections and individual critical alpha levels at 1.67% (α ≤0.0167), that will allow comparison of data at each time-point
[54]. The use of mixed ANCOVAs will help reduce within-group error variance, namely by controlling for baseline differences between participants in each condition and by taking into account possible confounds (for example, age, diagnosis, cancer stage), while providing a higher statistical power in detecting an intervention effect (
[55,56]).These intra-group analyses will serve to evaluate the impact of the mindfulness-based meditation intervention on quality of life, sleep, and mood pre-post intervention, as well as follow-up.

Specifically, changes in quality of life scores (as indicated by the Pediatric Cancer Quality of Life Inventory) between baseline, 8 weeks and 6 months will be tested. Similarly, a change in sleep quality scores (as indicated by the Pittsburgh Sleep Quality Index) and mood scores (as indicated by the Depression and anxiety scales of the Beck Youth Inventories and the PANAS-C) will be tested between baseline, 8 weeks and 6 months. These analyses will also serve to test secondary hypotheses, by allowing inter-group comparisons between the experimental group and the wait-list controls. Specifically, a difference in quality of life scores, sleep quality scores, and mood scores at baseline, 8 weeks, and 6 months will be assessed between groups.

Comparable analyses will be conducted on the data collected from the second experimental group once participants from the wait list condition go through the intervention. All statistical analyses will be conducted using SPSS version 20 (SPSS Inc., Chicago, IL, USA).

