### Primary aim

This article presents the rationale and protocol development for a research project aimed at evaluating the effects of a mindfulness-based meditation intervention on quality of life, sleep, and mood in adolescents with cancer compared to a control group. In light of data available on adult populations and emerging from research in youth, three hypotheses are formulated: (1) mindfulness meditation will have beneficial effects on the mood of adolescents completing this practice; (2) mindfulness meditation will have beneficial effects on quality of life of the participants; and (3) mindfulness meditation will have beneficial effects on sleep quality of the participants.

Specifically, significant improvements are expected to be observed in quality of life, mood, and sleep between pre-intervention and post-intervention measures in the experimental group. These effects should be sustained 6-months post-intervention.

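### Three ANCOVAs at 0.0167 cannot cover the five or six primary scores named, and no rule says how the mood scores combine into one test

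*Protocol article*

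**What the plan says.** Under Primary aim, "three hypotheses are formulated": one each for mood, quality of life and sleep.

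Under Planned statistical analyses, "The cut-point to reject the null hypothesis will be set at 5" per cent. The section continues: "Primary hypotheses will first be tested using three mixed analyses of covariance (ANCOVA) with Bonferonni corrections and individual critical alpha levels at 1.67" per cent.

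The same section then assigns instruments to the three domains. Quality of life and sleep have one instrument each, the Pediatric Cancer Quality of Life Inventory and the Pittsburgh Sleep Quality Index. Mood has several: "mood scores (as indicated by the Depression and anxiety scales of the Beck Youth Inventories and the PANAS-C) will be tested".

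Primary outcome measures lists all of these as primary. For the Beck Youth Inventories it describes depression and anxiety as two scales ("Both scales have presented excellent internal consistency"). For the PANAS-C it says "this measure is used to evaluate the presence and fluctuations in positive and negative emotions", without stating whether this yields one score or two.

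**The concern.** Three hypotheses, three analyses and a divisor of three agree with one another. The list of scores does not agree with them. A mixed ANCOVA with repeated measures still has one outcome variable, followed over time. Quality of life and sleep use two of the three analyses, which leaves one for mood, and mood has three named scores, or four if the PANAS-C is split.

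One ANCOVA could serve mood if the article defined a composite, chose a lead scale, or replaced the ANCOVA with a multivariate test. Several ANCOVAs could also serve it under a rule that every mood score must be significant. None of these is stated.

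Without such a rule, an analyst could run one model per mood score, hold each to 0.0167, and report a mood benefit from whichever score crosses the line. The mood hypothesis would then have three or four chances where the correction allows for one.

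**Working it through.** **Inputs from the article.** Overall alpha 0.05; three ANCOVAs at 0.0167 (Planned statistical analyses); three hypotheses (Primary aim); named scores (Primary outcome measures and Planned statistical analyses).

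**Assumptions, not in the article.** Tests are two-sided. Each score is tested once at 0.05/3. Any one significant score counts as success. Correlations between test statistics are not given, so a range is shown.

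**Step 1: reproduce the plan's figure.** 0.05/3 = 0.01667, which rounds to 0.0167. With exactly three tests the Bonferroni bound is 3 × 0.01667 = 0.0500, and under independence the error is 1 − (1 − 0.01667)³ = 0.0492. The correction works for three tests.

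**Step 2: count the scores.** Beck depression (1) + Beck anxiety (1) + PANAS-C (1 or 2) + quality of life (1) + sleep (1) = 5 or 6. Five is the minimum that the text supports.

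**Step 3: family-wise error at 0.05/3 per score.**

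- Bound: k × 0.05/3, giving 0.0833 for k = 5 and 0.1000 for k = 6.
- Independent: 1 − (1 − 0.05/3)^k, giving 0.0806 and 0.0959.
- Common correlation ρ: 1 − ∫ φ(u) [Φ((c − √ρ u)/√(1−ρ)) − Φ((−c − √ρ u)/√(1−ρ))]^k du, with c = Φ⁻¹(1 − 0.01667/2) = 2.394, integrated numerically.

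| Common correlation | Five scores | Six scores |
|---|---|---|
| 0 | 8.1% | 9.6% |
| 0.5 | 6.8% | 7.8% |
| 0.7 | 5.6% | 6.2% |
| 0.8 | 4.7% | 5.2% |
| 0.9 | 3.7% | 4.0% |

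With one correlation shared by every pair, including sleep and quality of life, the rate reaches 5% at about 0.77 for five scores and 0.82 for six.

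**Step 4: a more structured assumption.** Mood scores may correlate strongly with one another and less with sleep and quality of life. Simulation (1,000,000 draws per scenario) with correlations of 0 to 0.9 among mood scores, and 0 to 0.5 (never above the mood value) for all other pairs, gave 5.6% to 8.1% for five scores and 5.9% to 9.7% for six (simulation error puts the top of the last range just above the exact 9.6%). At 0.5 among mood scores and 0.3 elsewhere the values were 7.3% and 8.5%. Every scenario exceeded 5%.

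**Step 5: the mood hypothesis alone.** Its share is 1.67%. Three mood scores at 0.0167 each give 4.9% if independent and 4.5% at correlation 0.5. Four give 6.5% and 5.7%.

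**Step 6: thresholds that match the count.** 0.05/5 = 0.0100; 0.05/6 = 0.0083.

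**The case against.** The strongest reply is that the plan is internally consistent at the level of hypotheses and that the inflation is conditional. The article says three analyses, not five or six. A mood composite, a single multivariate mood test or an all-must-succeed rule would hold 5%, and a condensed article may leave such a rule to the full protocol or analysis plan, which is not shown. This stands in part: no definite error rate can be attributed to the trial. It does not remove the point. The article itself fixes the number of tests, their type, the per-test alpha and the scores to be tested, and these statements do not fit together.

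Three stronger readings are tempting, and the article does not support them.

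- A reader might call 0.0167 a miscalculation. It is not; the division is correct for three tests.
- A reader might take six scores as established. The PANAS-C is presented as one 20-item questionnaire and its scoring is not stated.
- A reader might double the count because scores are compared at 8 weeks and at 6 months. A mixed model can test time in one omnibus effect per score, and separate tests at each visit are only one reading of the text.

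Pilot status also carries weight. The article calls this a pilot, targets 28 participants, and under Pilot study endpoints treats the analyses as indications of benefit, with effect sizes as the measure. That lowers the severity. It does not excuse the mismatch, because the plan still sets a 5% cut-point and a Bonferroni correction for its primary hypotheses.

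**Conclusion.** The point holds as a mismatch between the stated number of tests and the named primary scores, caused by an undefined mood endpoint. It should be fixed; in a pilot it is not critical.

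Its size is conditional. If each score is tested once at 0.0167 and any one counts, the family-wise error is 8.1% for five scores or 9.6% for six under independence, and 6.8% or 7.8% at a common correlation of 0.5. By 0.7 the excess is small (5.6% or 6.2%). It disappears only if all scores, sleep and quality of life included, correlate at roughly 0.8 or more. The article gives no correlations, and a stated 5% level should not depend on them.

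**What to change.** Before the data are analysed, choose one of two routes.

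1. **Define one mood test.** Name one mood score as primary, or one pre-defined mood composite or multivariate mood test. Keep exactly three tests at 0.0167 and report the other mood scores as secondary.
2. **Keep all scores primary.** State whether the PANAS-C gives one score or two, specify one test per score, and apply Holm or Bonferroni over the actual number. The first threshold is 0.0100 for five scores or 0.0083 for six.

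Neither route requires moving the 6-month assessment out of the primary hypotheses, since Primary aim expects effects to be sustained to that point. One pre-specified effect per score can cover it.

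The change is to wording only; no data collection is affected. The first route costs some primary outcomes. The second costs power. As an illustration, take a two-sided two-sample t-test with 28/2 = 14 per arm and an assumed standardised difference of 0.5 (noncentrality 0.5 × √(14/2) = 1.32, 26 degrees of freedom). Power is about 13% at 0.0167, 9% at 0.0100 and 8% at 0.0083. A mixed ANCOVA would give different values, but the direction is the same. With power this limited, the first route is the more economical.
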